### Process evaluation

In a process evaluation we will assess facilitators and barriers that influence the implementation process and adoption of the SDM strategy, making use of existing frameworks for the implementation of SDM [44–46]. This evaluation will also yield more in-depth information about relevant contextual factors and experiences of patients and healthcare providers (i.e. physicians and nurses) with the SDM strategy in general and with the DAs more specific. For this purpose, we will organize focus groups with patients and healthcare providers.

### Statistical methods

Baseline characteristics will be described using descriptive statistics. If continuous, Student’s t-test will be used to calculate differences between clusters for normally distributed data. Mann–Whitney U-test will be used for skewed data.

Mixed models will be used to analyse the data from the stepped-wedge design and to account for clustering of patients within hospitals at different follow-up periods. We will analyse the effect of the intervention in comparison with usual care on the primary outcome surgery rates. We will adjust for confounding factors, such as age, sex, clinical parameters (e.g. comorbidity), and working and social activities. Furthermore, we will use mixed models to analyse the effect of the SDM strategy regarding the secondary outcomes and to account for clustering of repeated measurements within patients and clusters of patients within hospitals. In addition, we will include time as a covariate in order to investigate time trends. When applicable, we will test assumptions of normality and linearity, and interaction terms.

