### Design

The E-valuAID is a multicentre, non-randomized stepped-wedge study in patients with an inguinal hernia, gallstones, knee- or hip osteoarthritis. The DAs will be implemented stepwise in six surgical and six orthopaedic departments in the Netherlands. Departments implement the DAs at different timepoints and will have different control and intervention periods. Therefore, the stepped-wedge design allows for comparisons within and between departments, and comparisons over time (Fig. 1). Three additional control hospitals will be included to investigate time trends in surgery rates for both surgical and orthopaedic departments across the entire study, without implementing DAs. Data collection began on July 1, 2020, and each centre will include consecutive eligible patients for two years (Fig. 1).

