### Implementation

Implementation of the SDM strategy is in accordance with a standardized protocol, which consists of four steps: (1) preparation, (2) instruction, (3) implementation of the DA and (4) evaluation.During preparation, a local project group is assigned, including a physician, nurse practitioner, front- and back-office support, representative of the communication- and quality control department and the local project leader of the study. The group is responsible for setting goals, defining key results and identifying the clinical pathway of patients.The instruction consists of 3 workshops for healthcare providers and desk employees to inform about SDM and to give instruction on the use of the DAs.Implementation of the online DA executed by the local project group under supervision of the project leader of the study.During evaluation, all stakeholders from the participating department are asked about their experiences with the SDM strategy.

Implementation at different departments will be performed after time intervals of 3 months and within a time window of 2 weeks. After 18 months, all departments will work according to the SDM strategy, patient inclusion will continue for another 6 months. For an overview of the stepped-wedge design and implementation scheme, see Fig. 1.

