### Rationale of the study design

In the present study we chose a pragmatic approach to investigate the effectiveness of SDM with an online DA. A recent systematic review shows that the stepped-wedge design is particularly used for practical and methodological purposes, which makes it well-suited for this study [48]. For example, as only a limited number of clinics start simultaneously, this design allows a thorough implementation of the intervention in each clinic. The implementation protocol requires a dedicated introduction of SDM to the users by providing information about the study and the online DA. Moreover, the design allows for evaluation of both the effect on surgery rates on a hospital level and outcomes on a patient level. An alternative design of a randomized trial on patient-level would have the potential pitfall of contamination of usual care by the intervention strategy, as it is conceivable that specialists transfer their SDM experience and methods to usual care. Cluster randomization of departments appeared not feasible during the explorative discussions with participating hospitals. They strongly preferred to start the implementation of the SDM strategy at a predetermined moment in time, and our logistic inability to implement randomly decided to refrain from cluster randomization. In the present design, the potential risk of selection bias, due to clinicians’ decision of not providing an SDM strategy is negligible, as all consecutive patients receive a DA before their first consultation.

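### Start order is not randomised, so the mixed models should use fixed department effects; a random hospital intercept would let stable differences in department level leak, modestly, into the effect estimate

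*Protocol article*

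**What the plan says.** The Design section calls the study a "multicentre, non-randomized stepped-wedge study in patients with an inguinal hernia, gallstones, knee- or hip osteoarthritis" and notes that "the stepped-wedge design allows for comparisons within and between departments, and comparisons over time". On how start dates arose, Rationale of the study design reports that cluster randomisation was not feasible. Of the hospitals it says "They strongly preferred to start the implementation of the SDM strategy at a predetermined moment in time", and it adds that the team could not logistically implement in random order.

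For the analysis, Statistical methods states: "Mixed models will be used to analyse the data from the stepped-wedge design and to account for clustering of patients within hospitals". Adjustment is planned for patient-level confounders. After the sentence on secondary outcomes comes "we will include time as a covariate in order to investigate time trends". No fixed hospital or department term is mentioned, and no estimate restricted to within-department change. The Rationale section does discuss selection bias, but only the kind that would arise if clinicians withheld the aid from individual patients.

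**The concern.** A random-intercept model treats department levels as draws unrelated to the intervention schedule. Randomising the order would justify that; here nothing in the design does. If early starters tend to have higher surgery rates, part of that difference enters the estimate and the reduction is understated. If they tend to have lower rates, the reduction is overstated. The direction cannot be known in advance, and the listed patient-level covariates do not capture department practice style. The Background gives practice variation as part of the study's motivation, so differences in level are to be expected.

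The primary effect is at stake, and more so the patient-reported outcomes. Fewer patients per department and quarter make a random-intercept model lean more on comparisons between departments.

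**Working it through.** **Inputs from the Protocol article.** Six departments per condition; 3-month steps; all switched by month 18, then 6 more months, so 8 quarters; ICC 0.10; 50, 45, 120 and 95 patients per department-quarter (hernia, gallstones, knee, hip); assumed reductions of 10, 10, 5 and 7%.

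**Stated totals.** n × 6 × 8 gives 50 × 48 = 2400, 45 × 48 = 2160, 120 × 48 = 5760 and 95 × 48 = 4560. All four match the Sample size section.

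**Assumptions.** One department switches per quarter (Fig. 1 is not shown), so departments 1 to 6 have 7, 6, 5, 4, 3 and 2 intervention quarters. Cells are equal in size, quarter is categorical, reductions are absolute, and the scale is linear probability. No baseline rate is stated. The Woertman formula returns the stated n at baselines of about 64, 73, 85 and 70%, and these are used only to convert to percentage points.

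**Formulas.** Let s = (1 − ICC)/n and k = s/(s + 8 × ICC), where k is the weight the random-intercept model gives to between-department information.

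- Total treatment contrast after removing quarter means: (5 + 8 + 9 + 8 + 5)/6 = 5.833.
- Between-department part: 8 × Σ((3.5 − i)/8)² = 17.5/8 = 2.1875.
- Within-department part: 5.833 − 2.1875 = 3.646.
- Leak, as a share of an evenly spaced first-to-last gap in level: 3.5k/(3.646 + 2.1875k).
- Variance increase from fixed department effects: 2.1875k/3.646 = 0.6k.

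With fixed department effects the between part drops out and the leak is exactly zero.

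**Hernia, ICC 0.10.** s = 0.9/50 = 0.018; k = 0.018/0.818 = 0.0220. Leak = 0.0770/3.694 = 2.1%. Variance increase = 0.6 × 0.0220 = 1.3%. The SD of department levels is √(0.10 × 0.241) = 15.5 points, so six evenly spaced, fully ordered levels span 41.5 points. Bias = 0.0208 × 41.5 = 0.87 points.

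| Condition | k | Leak | Gap, points | Worst-case bias, points | % of effect | SE, points | Variance increase |
|---|---|---|---|---|---|---|---|
| Hernia | 0.0220 | 2.1% | 41.5 | 0.87 | 8.7 | 3.43 | 1.3% |
| Gallstones | 0.0244 | 2.3% | 39.4 | 0.91 | 9.1 | 3.43 | 1.5% |
| Knee | 0.0093 | 0.9% | 31.9 | 0.28 | 5.7 | 1.71 | 0.6% |
| Hip | 0.0117 | 1.1% | 39.8 | 0.44 | 6.4 | 2.39 | 0.7% |

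The table takes the SD of the six levels with divisor 5 and the binomial variance at the mid-point rate. With divisor 6 and the variance at the baseline rate, the biases are about 0.92, 0.95, 0.29 and 0.47 points. Hence the range of about 0.3 to 0.95 points, or 0.2 to 0.3 SE. Coverage in the tabulated case stays at about 94 to 95%. Bias scales with the correlation between level and order, so 0.5 halves it.

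**Lower ICC.** At 0.02, hernia has k = 0.0196/0.1796 = 0.109 and a leak of 9.8%. Across conditions the worst-case bias is about 0.7 to 2.0 points. Fixed effects then raise the SE by 1.5 to 3.5%.

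**Questionnaire outcomes.** The documents give no responder numbers or ICC. Assuming 15 to 25 responders per department-quarter and ICC 0.02 to 0.05, worst-case bias is 0.05 to 0.10 SD and the variance increase 5 to 17%.

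**Three control hospitals in the model.** Taking them at the average level, with n as planned, worst-case primary bias is 0.2 to 0.6 points and the variance increase 1.2 to 3.1%. Their own level is not randomised either. For hernia about 3.4% of any difference between implementing and control hospitals leaks, roughly 0.5 points per SD (0.034 × 15.5).

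**Department-specific linear trends on top of fixed effects.** Variance rises by about 10% with six departments and about 68% with the control hospitals.

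**The case against.** The article does not write out a random hospital intercept. A model with fixed departments and random patient or department-by-period effects is also a mixed model and fits the sentence, which goes on to mention follow-up periods. The choice could be made in an analysis plan that is not shown. This stands as a limit: the criticism applies to the ordinary reading of the text. It does not remove the point, because the article states both a non-random order and a model class whose usual form relies on random order.

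A reader might infer that hospitals picked their dates according to how often they operate. The documents do not say so. They cite a preference for a predetermined start together with logistics, do not say who set each date, and report no link between order and surgery level. Either reason leaves the order non-random, but the correlation itself is unknown.

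It is also fair that the planned contrast in Effect evaluation is before versus after implementation. At the planned cell sizes a random-intercept estimate is already almost wholly within-department. That is why the primary bias is small at ICC 0.10, and equally why fixed effects cost so little.

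**Conclusion.** The point holds as a modest weakness in the choice of analysis that is cheap to repair. For the primary outcome at the protocol's ICC, even complete ordering of departments by level gives only about 0.3 to 0.95 points of bias, 6 to 9% of the assumed effects. The larger figures depend on a lower ICC than planned, or on response numbers the documents do not give. All figures in points rest on back-solved baselines; the leak percentages and variance costs do not.

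A reader might conclude that the primary result will be seriously biased. The numbers do not support that. A reader might also think fixed effects make the comparison safe from non-random ordering altogether. They remove stable differences in level only; trends that differ between early and late departments would remain.

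**What to change.** In Statistical methods, specify department as a fixed effect together with quarter effects in each condition's surgery-rate model. Do the same in the secondary-outcome models, keeping random effects for repeated measures within patients. State that the estimate rests on within-department change, and say whether the control hospitals enter the model. Pre-specify department-specific linear trends as a sensitivity analysis only.

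This changes analysis wording and nothing in conduct. At ICC 0.10 with six departments, primary power falls by about 0.2 to 0.6 percentage points from roughly 83% at the back-solved baselines. The larger costs are those shown above for sparse questionnaire data and for the trend analysis. The 68% variance increase with control hospitals is the reason not to make the trend model primary.

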#### Safety monitoring and data access

Data will be captured and stored in an online registry (Castor EDC) during the control phase. During intervention phase, answers to questionnaires and in DAs will be stored in a second secured environment, which is password protected and can only be accessed by investigators. All data will be stored pseudonymized. Locking of data and code list will take place after the end of follow‐up of the last included patient, and data will be stored for 15 years. Data management will be performed in accordance with FAIR guiding principles [47].

#### Ethical consideration

The protocol of the study was registered under file number 2018-4815 and assessed by the Central Committee on Research Involving Human Subjects of Arnhem-Nijmegen (CCMO Arnhem-Nijmegen). The committee confirmed the Medical Research Involving Human Subjects Act (WMO) does not apply. Local ethics assessment committees of the participating hospitals are requested to approve the protocol as well.

## Discussion

The results of the E-valuAID will clarify if the implementation of an SDM strategy with online DAs in surgical- and orthopaedic practices reduces surgery rates and is cost-effective compared to usual care. This multicentre study with a stepped-wedge design will show the effect of an SDM strategy on surgery rates, patient-reported outcomes, and cost-effectiveness. We hypothesize that the application of DAs will result in lower surgery rates, while improving patient-reported outcomes.

### Rationale of the study design

In the present study we chose a pragmatic approach to investigate the effectiveness of SDM with an online DA. A recent systematic review shows that the stepped-wedge design is particularly used for practical and methodological purposes, which makes it well-suited for this study [48]. For example, as only a limited number of clinics start simultaneously, this design allows a thorough implementation of the intervention in each clinic. The implementation protocol requires a dedicated introduction of SDM to the users by providing information about the study and the online DA. Moreover, the design allows for evaluation of both the effect on surgery rates on a hospital level and outcomes on a patient level. An alternative design of a randomized trial on patient-level would have the potential pitfall of contamination of usual care by the intervention strategy, as it is conceivable that specialists transfer their SDM experience and methods to usual care. Cluster randomization of departments appeared not feasible during the explorative discussions with participating hospitals. They strongly preferred to start the implementation of the SDM strategy at a predetermined moment in time, and our logistic inability to implement randomly decided to refrain from cluster randomization. In the present design, the potential risk of selection bias, due to clinicians’ decision of not providing an SDM strategy is negligible, as all consecutive patients receive a DA before their first consultation.

### Current evidence for SDM in surgery

Although the effect of SDM and provision of DAs on patient satisfaction are promising [49, 50], there is a knowledge gap on the impact of SDM-instruments in terms of cost-effectiveness. Up to date, no trials are performed to evaluate the cost-effectiveness of DAs in patients with an inguinal hernia or gallstones. One study evaluated the impact of a DA consisting of a 50 min video and a booklet in 343 patients with knee- or hip osteoarthritis. This RCT showed DAs were cost-effective, with similar health outcomes [51]. Furthermore, Stacey et al. reviewed the literature in 2017, and they included four trials with 570 patients with knee or hip osteoarthritis [40, 41, 52, 53]. These studies assessed various effects of a DA: patient knowledge, the efficiency of decision-making, or wait times between screening and definitive choice, but not on cost-effectiveness. Only our retrospective evaluation on the effect of online DAs in patients with an inguinal hernia or cholecystolithiasis suggested a reduction in surgical interventions, but a cost-effectiveness analysis was lacking [39]. In the absence of existing evidence, it is clear that more knowledge on the benefits of SDM from patient and societal perspectives is necessary. The E-valuAID aims to solve the current void in the literature on the benefits of SDM and online DAs. Results of the present study as proposed here, will affect healthcare policy concerning decision-making in surgery for the coming decades.

In conclusion, SDM is eminently applicable in patients with an inguinal hernia, gallstones, knee- or hip osteoarthritis due to both a surgical and conservative treatment option. This study will show whether an SDM-strategy will lead to a reduced surgery rate and if future implementation is cost-effective.

## Data Availability

Not applicable.

## Abbreviations

CEA: Cost-effectiveness analysis
CUA: Cost-utility analysis
CONSORT: Consolidated standards of reporting trials
DA: Decision aid
EMR: Electronic medical record
EQ-5D-5L: EuroQol-5D-5L
GSL: Gallstone symptom list
HOOS-PS: Hip disability and Osteoarthritis Outcome Score—Physical function Short form
IPDAS: International patient decision aid standards
KOOS-PS: Knee injury and Osteoarthritis Outcome Score—Physical function Short form
NTR: Netherlands Trial Register
QALY: Quality-adjusted life-year
SDM: Shared decision-making
SF-HLQ: Short Form—Health and Labour Questionnaire
WMO: Wet Wetenschappelijk Medisch onderzoek, Medical research involving human subjects act
